### Handling missing data

A member of the research team will contact patients for any missing data (eg, questionnaires) via telephone and post. Where patients attend for follow-up clinic, the potential for missing data will again be limited. Imputation of missing responses is not proposed for patient-reported outcomes as this is not a definitive trial and no hypothesis testing will be performed.

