### Secondary objectives

Integration of the intervention into the clinical pathway by time from decision to operate from study recruitment.Explore barriers to study recruitment, including descriptive reasons for non-participation from screening logs.Fine-tune study procedures and pilot data capture forms aiming for over 90% completion of important perioperative data for each patient.To assess the proportion of patients in the INT group who have quit smoking by the day of surgery and 1 month after surgery.To assess the proportion of patients in the observation only UC group who have quit smoking by the day of surgery and 1 month after surgery.To define the variability of smoking cessation practices in all patients using the nicotine replacement usage questionnaire.Qualitative interview: to understand patients’ experiences of and engagement with the intervention, and any unintended consequences; to establish whether the intervention is acceptable to thoracic surgery patients and staff and investigate recommendations for optimisation of intervention delivery.

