INT patients will receive proactive support within 2 days of the quit date (in person or by telephone) and then weekly until 1 month after surgery. The weekly sessions will concentrate on facilitators and barriers to quitting, relapse, pharmacotherapy side effects and withdrawal symptoms. Face-to-face interactions will occur during the surgical outpatient appointments, preclerking clinic and during hospital admission to reduce the number of additional visits. If patients are unable to attend face-to-face visits, videoconferencing or telephone visits will be attempted. Thus, the INT will fit into the ‘referral to treatment’ target time frame and ensuring surgery is not delayed as recommended by NICE.

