## Outcome and data collection

### Patient recruitment into study

The overall aims of the feasibility are to find out if a larger trial is feasible. The quantitative measurements related to this include the following:

Proportion of all elective thoracic procedures screened.Proportion of eligible participants of those screened.Proportion of eligible participants consented to receive intervention.

In this feasibility study, selecting five units whose overall elective thoracic patient throughput amounts to 4000 patients a year, of whom 20% are smokers and 20% agree to take part in the study. It is expected that 60 eligible patients will be recruited to the INT group and 60 patients to the UC group of the study, with recruitment of 120 patients in total. Therefore, the aim is to recruit five patients a month to each group over the 12 months recruitment period across all sites.

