### Smoking-related outcomes

In this study, the feasibility of the following questionnaires will be tested:

Self-reported quit rate and exhaled CO measurement.Fagerstrom Test for Nicotine Dependency: assessment of nicotine addiction.^34^
Mood and Physical Symptoms Scale: assessment of cigarette withdrawal symptoms over the past 24 hours, including the strength of urge to smoke.^35^
Generic health-related quality of life (EQ-5D-5L): assessment to provide a preference-based measure of health-related quality-of-life.^36^
NRT and support usage questionnaire.Health resource usage questionnaire: assessment of resource will be assessed via patient-recall with resources being measured including planned hospital overnight stays, planned hospital outpatient visits, hospital emergency visits, hospital admissions, GP and other community service visits.

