### Data analysis

Appropriate summary statistics (eg, proportions and interquartile ranges, means and SDs) will be generated for the study feasibility and patient/clinical measures. Between-group measures (mean differences) will be generated alongside 95% CI; however, formal hypothesis testing will not be carried out as the aim here is not to conclusively prove efficacy and furthermore the size of sample is too small for any inferential tests to be meaningful. Participants will be kept in the groups they were allocated, regardless of compliance with treatment (intention-to-treat protecting against attrition bias). Analysis will be completed once all participants have completed all follow-up assessments. All data used in publication will be in an anonymous format in order to maintain patient study participation confidential.

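### The no-imputation rule makes self-reported quit rates available-case, and intention-to-treat does not protect them against attrition bias as the protocol claims

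*Protocol article*

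**What the plan says.** Under Handling missing data the protocol states: "Imputation of missing responses is not proposed for patient-reported outcomes as this is not a definitive trial and no hypothesis testing will be performed". The same section plans telephone and postal contact to recover missing items.

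Under Smoking-related outcomes, the list of questionnaires to be tested opens with "Self-reported quit rate and exhaled CO measurement". Under Data analysis, keeping participants in their groups whatever their compliance is described as "intention-to-treat protecting against attrition bias".

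The quit proportions are secondary objectives. For INT the wording is "To assess the proportion of patients in the INT group who have quit smoking by the day of surgery and 1 month after surgery", and a parallel objective covers UC. The Sample size calculation section justifies 60 INT patients partly by estimating the proportion quit by the day of surgery, and says the study will inform the sample size of a larger trial. No section gives an expected missing rate, or a denominator for the quit proportion when status is unknown.

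**The concern.** A quit rate depends heavily on how patients of unknown status are counted. The rule forbids imputing patient-reported outcomes, and counting an unknown as a smoker is a single imputation. Read literally, the plan therefore divides known quitters by those who answered.

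The reason given for the rule does not support it. Bias in a point estimate does not depend on whether a test is done, and point estimates with confidence intervals are what this study is meant to deliver. The only safeguard named is intention-to-treat, which deals with non-compliance and changes of treatment. It cannot supply an outcome that was never recorded.

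At stake are the quit proportions carried into the design of the definitive trial. The primary objective, the proportion of eligible patients who agree to take part, is not affected.

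**Working it through.** **Does the rule reach quit status?** Self-reported quitting is a patient's own report and is listed with the questionnaires, so on its face it does. Exhaled CO is a measurement, so the rule does not govern it. The protocol does not say which of the two defines quitting.

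**Where could status be missing?** Table 1 schedules self-report and CO at baseline, day of surgery, discharge, 1 month after surgery and 6 months after enrolment, for both groups. On the day of surgery the patient is in hospital. Of the two time points in the quit objectives, 1 month is the exposed one.

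**Inputs**
- Group size: 60 (Patient recruitment into study; Sample size calculation).
- Illustrative quit rate: one in three, the background self-reported rate at lung cancer surgery given in the Introduction. It is not a planning value.
- Missing fraction m: not stated; 10%, 20% and 30% are assumed.
- Quit rate among patients with missing status, q: not stated; varied below.

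**The plan's nearest figure.** The protocol expects 95% CI widths of 10% to 20% for recruitment and compliance rates. The Wald full width is 2 × 1.96 × √(p(1−p)/n). At n = 60 it is 15.2% for p = 0.10, 20.2% for p = 0.20 and 23.9% for p = 1/3. No p is stated, so the range cannot be checked exactly. It serves here as a yardstick: a quit rate near one third carries about ±12 points of sampling error.

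**Case 1: no non-responder has quit.** With 20 quitters among 60, the true rate is 20/60 = 33.3%, and the responder-only rate is 20/(60(1−m)):
- m = 10%: 20/54 = 37.0%, 3.7 points too high
- m = 20%: 20/48 = 41.7%, 8.3 points too high
- m = 30%: 20/42 = 47.6%, 14.3 points too high

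If every non-responder had instead quit, the rates over all 60 would be 26/60 = 43.3%, 32/60 = 53.3% and 38/60 = 63.3%.

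**Case 2: other quit rates among non-responders.** Fix the observed responder rate at 1/3. The bias is then m × (1/3 − q):
- m = 20%: +6.7 points if q = 0, +3.3 if q = 1/6, 0 if q = 1/3, −3.3 if q = 1/2
- m = 30%: +10.0, +5.0, 0 and −5.0 points for the same values

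**Illustration for the next trial.** Assume true rates of 20% and 33.3%, two-sided 5%, 90% power, individual-level comparison (no cluster adjustment). With p̄ the mean of p₁ and p₂ and d their difference, n per arm = [1.960√(2p̄(1−p̄)) + 1.282√(p₁(1−p₁)+p₂(1−p₂))]² / d².
- True rates: [1.960√0.3911 + 1.282√0.3822]² / 0.1333² gives 230.
- With 20% missing in both arms, all smoking, the responder rates are 0.20/0.8 = 25% and 0.333/0.8 = 41.7%: [1.960√0.4444 + 1.282√0.4306]² / 0.1667² gives 167.
- The shortfall is (230 − 167)/230 = 27%.

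**The case against.** The protocol never states that the denominator is responders, and it refers to a statistical analysis plan that is not shown. A missing denominator alone would be no finding. But this is a written rule with a written reason, and an analysis plan that counted unknowns as smokers would contradict it.

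The protocol also limits the exposure. It chases missing data and aims for over 90% completion of important perioperative data. If that target covers quit status, which is not said, the worst case near a one-third rate is about 3.7 points against ±12 points of sampling error. That is a fair limit on the day-of-surgery estimate and a weaker one at 1 month.

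A reader might go further and infer three things that the documents do not support:
- That the quit rates are bound to be too high. The direction depends on non-responders quitting less often than responders. This is plausible, but the protocol gives no data on it.
- That missingness is bound to differ between groups, because INT patients have weekly contact. It may differ, but both groups share the same self-report and CO schedule, and the plan to chase missing data is not limited to one group.
- That remote contact removes the CO readings. The sentence "If patients are unable to attend face-to-face visits, videoconferencing or telephone visits will be attempted" concerns INT support sessions, not the outcome assessments in Table 1.

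It can also be said that retaining non-compliers does prevent the bias from excluding them. That is true, but it is not attrition bias in the sense of missing outcomes.

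**Conclusion.** The point holds in a limited form. The protocol bars imputation for self-reported quit status, gives a reason that does not justify doing so, and credits intention-to-treat with a protection it does not provide. The resulting proportions are available-case and may be biased, most plausibly upward and mainly at 1 month.

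The size can only be ranged. It is 3.7 to 14.3 points at a true 33.3% with 10% to 30% missing, assuming no non-responder has quit. It is smaller if some have, nil if they quit as often as responders, and reversed if more often. The sample-size illustration rests on further assumed rates and shows only that the error can carry forward. Because the quit rates are secondary objectives of a feasibility study, this should be corrected but does not threaten its main purpose.

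**What to change.** - Exempt the quit outcomes from the no-imputation rule. The other questionnaires can stay as they are.
- Use as denominator all enrolled patients in the group who are alive at the time point. For the day of surgery, use those who have surgery and count the others separately. Count missing status as smoking.
- Report responder-only and best/worst-case rates as sensitivity analyses.
- Report self-reported and CO-verified rates separately, so that a patient who reports abstinence but has no reading is visible and not silently reclassified. Show missingness by group and time point.
- Delete "intention-to-treat protecting against attrition bias" from Data analysis.

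The cost is one analysis rule and one table, with no extra patients or data. The downside is that headline quit rates will be lower and may understate quitting where some non-responders have stopped. Missing-as-smoking is itself untestable, and the sensitivity analyses show how much depends on it.

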## Data management and quality assurance

### Data management and confidentiality

Personal data will be collected from trial participants and hospital notes on CRFs, coded with the participant’s unique trial number and initials. This will be held securely and strictly confidentially according to NHS policies. Patients in the semistructured qualitative interviews will be consented specifically for their name, address and contact telephone number to be shared with University of Birmingham (UoB) and University College London. Data will be transferred securely by encrypted end-to-end email and will not be labelled with private identiﬁable information. Interview response information will be kept encrypted on a computer in a locked ofﬁce. No data that could be used to identify an individual will be published. Data will be stored on a secure server under the provisions of the Data Protection Act and/or applicable laws and regulations. Data may be accessed by external regulatory agencies and the Study Sponsor representatives and permission for this access will be documented within the participants consent form.

### Monitoring and audit

Onsite monitoring will be conducted as required by the UoB Clinical Research Compliance Team, with activities reported to the trials team and any issues noted followed-up to resolution. Additional onsite monitoring visits may be triggered, for example, by poor CRF return, poor data quality, low adverse event (AE) reporting rates, excessive number of participant withdrawals/deviations. Study data and evidence of monitoring and systems audits will be made available for inspection by the regulatory authority as required.

### Long-term storage of data

Trial data will be stored archived after the formal closure of the trial in accordance with archive policy and for the appropriate duration as per current legislation.

### Data access

On completion and publication of the study, individual participant data will be shared that underlie the results reported in study after deidentification. Additional related documents will be available including the study protocol, statistical analysis plan an analytical code. This data will be available in the beginning 3 months and 5 years following article publication to those who provide a methodologically sound proposal for analysis to achieve the aims in the approved proposal. All proposals should be directed to [contact]. To gain access, requestors will need to sign a data access agreement. Data will be available for 5 years at a third-party website.

## Sponsorship and indemnity

The UoB will act as the sponsor for this study. Delegated responsibilities will be assigned to the Chief Investigator and the NHS Trusts involved in the study. The UoB has in force a Public Liability Policy and/or Clinical Trials policy, which provides cover for claims for ‘negligent harm’ and the activities here are included within that coverage.

## Ethics and dissemination

This study has obtained ethical approval from the NHS West Midlands Black Country Research Ethics Committee (Protocol V.3.0; REC number 19/WM/0097). This aim of this feasibility study is to inform a substantive trial. On completion, results will be published in a peer-review scientific journal.
